## Abstract

**Background:**

Depression during pregnancy is a common and high impact disease. Generally, 5–10 % of pregnant women suffer from depression. Children who have been exposed to maternal depression during pregnancy have a higher risk of adverse birth outcomes and more often show cognitive, emotional and behavioural problems. Therefore, early detection and treatment of antepartum depression is necessary. Both psychotherapy and antidepressant medication, first choice treatments in a non-pregnant population, have limitations in treating depression during pregnancy. Therefore, it is urgent and relevant to investigate alternative treatments for antepartum depression. Bright light therapy (BLT) is a promising treatment for pregnant women with depressive disorder, for it combines direct availability, sufficient efficacy, low costs and high safety, taking the safety for the unborn child into account as well.

**Methods:**

In this study, 150 pregnant women (12–18 weeks pregnant) with a DSM-V diagnosis of depressive disorder will be randomly allocated in a 1:1 ratio to one of the two treatment arms: treatment with BLT (9.000 lux) or treatment with dim red light therapy (100 lux). Both groups will be treated for 6 weeks at home on a daily basis for 30 min, within 30 min of habitual wake-up time. Follow-up will take place after 6 weeks of therapy, 3 and 10 weeks after end of therapy, at birth and 2, 6 and 18 months postpartum. Primary outcome will be the average change in depressive symptoms between the two groups, as measured by the Structured Interview Guide for the Hamilton Depression Scale – Seasonal Affective Disorder version and the Edinburg Postnatal Depression Scale. Changes in rating scale scores of these questionnaires over time will be analysed using generalized linear mixed models. Secondary outcomes will be the changes in maternal cortisol and melatonin levels, in maternal sleep quality and gestational age, birth weight, infant behaviour, infant cortisol exposure and infant cortisol stress response.

**Discussion:**

If BLT reduces depressive symptoms in pregnant women, it will provide a safe, cheap, non-pharmacological and efficacious alternative treatment for psychotherapy and antidepressant medication in treating antepartum depression, without any expected adverse reactions for the unborn child.

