### BLT and depression during pregnancy

The SCN generates the circadian rhythms in physiology and behaviour, including reproductive hormones. Pregnant women typically show disturbed, desynchronised circadian rhythms, resulting in disturbed sleep patterns, which puts them at risk for depression [39]. Moreover, disturbed sleep and decreased physical condition put pregnant women at risk for decreased activity and less exposure to daylight [40], which might further enhance their risk for depression.

Two small (*n* = 10 and *n* = 27) randomized controlled trials among pregnant women with non-seasonal depression showed significant improvement of depression among women exposed to BLT compared to placebo [41, 42]. Treatment effect in terms of mean improvement of depressive symptoms was comparable with the effects of antidepressant medication (effect size around 0.45), making it a competitive treatment for antepartum depression, but without the possible adverse effects of medication to the unborn child. Although these studies provide evidence for the effectiveness of BLT for depression during pregnancy, their sample size is small.

While in previous studies among elderly patients cortisol and melatonin rhythms normalized after BLT treatment [23], the question is whether improvement of depressive symptoms after BLT in pregnant women is also mediated through improved endocrine functioning or whether these symptoms are primarily determined by the physiology of pregnancy itself. Therefore, we will also examine the circadian rhythms and hormone levels of the pregnant women, to study whether BLT also effects endocrine functioning during pregnancy.

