### Adverse effects

At every measurement, we will ask for adverse effects. The adverse effects of BLT, such as headache and nausea, are generally mild and short-lived [58, 59]. A switch to hypomania is a more serious adverse effect, which would require effect managing. In a study exploring the side effects of short-term 10,000 lux light therapy in 70 patients suffering from SAD, 1 subject experienced hypomania [58]. In the two studies (*n* = 10 and *n* = 27) studying the effects of light therapy in a pregnant population, 1 subject showed hypomanic symptoms [41, 42]. If a participant shows hypomanic symptoms, the daily treatment duration will be reduced. This enhances the clinical safety [41].

No adverse effects for the foetus will be expected [42, 56].

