### Birth outcomes

After birth (T4), information will be obtained regarding complications during delivery and childbirth from the medical records: hypertension, pre-eclampsia, delivery aspects (duration, start with or without induction, augmentation, method of pain relief if any, instrumental delivery, caesarean section, hospital admission) and first week complications after delivery.

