#### Covariates

Potential covariates for the mother are psychiatric history, ethnicity, level of education, parity, gestational age (duration of pregnancy at study entry), substance use, chronotypes, duration of actual depression and other psychiatric or psychotherapeutic treatment interventions. These factors might affect depressive symptoms during pregnancy. After pregnancy, we will additionally correct for complications during delivery, breastfeeding and objective and subjective sleep parameters, since these factors might influence depressive symptoms after delivery.

Potential covariates for the infant are head circumference, congenital malformations, Apgar-score and neonatal admission at Neonatal Intensive Care Unit.

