## Discussion

We have presented a protocol for an RCT of light therapy for antepartum depression. Two earlier conducted RCT’s have shown the effects of BLT in pregnant women with depression, but studied only a small sample size (*n* = 10 and *n* = 27) [41, 42]. In this trial, we will study the effects of BLT on antepartum depression in a larger sample (*n* = 150) and in addition to the earlier conducted studies, we will not only study the effects of BLT on the mother, but on the infant as well. Moreover, we will study the effects of BLT on maternal endocrine levels and maternal circadian rhythm.

BLT will benefit pregnant women, for they will receive immediate treatment for their depressive symptoms. Psychotherapists are not always available, which would postpone treatment. Also, antidepressant medication is not immediately effective. However, BLT may be effective in as little as 1 week [55]. Moreover, the adverse effects of BLT are mild and short-lived.

The unborn child would benefit from this alternative treatment, for BLT does not cause adverse effects in the unborn child. Also, since BLT may be effective in a short time period, the risks associated with maternal depression (such as lower birth weight) may be diminished.

BLT would benefit society, since BLT has lower costs than treatment with antidepressant medication or psychotherapy.

Finally, since this RCT would be the first to study the effects of BLT in the infant, it would contribute to the understanding of the role of BLT, depression and the maternal HPA-axis in the developing foetus.

Thus, if BLT reduces depressive symptoms in pregnant women, it will provide an alternative, non-pharmalogical treatment for psychotherapy and antidepressant medication in treating antepartum depression. BLT combines direct availability, sufficient efficacy, low costs and high safety, taking the safety for the unborn child into account as well. Moreover, it does not require good language skills and it can be administered at home. These considerations make BLT for treating depression in pregnant women relevant, especially in urban multi-ethnic populations with high prevalence of depression and a low level of personal resources.

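### Foetal safety is stated as fact and tied to the mood result, while congenital malformations, Apgar score and NICU admission are named only as potential covariates

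*Protocol article*

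**What the plan says.** **The safety statements.** The abstract's Discussion reads: "If BLT reduces depressive symptoms in pregnant women, it will provide a safe, cheap, non-pharmacological and efficacious alternative treatment". The sentence ends with a qualifier on the child: "without any expected adverse reactions for the unborn child". The Adverse effects section likewise gives only an expectation for the foetus, citing references 42 and 56. The main Discussion drops the hedge: "BLT does not cause adverse effects in the unborn child".

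**The evidence described.** The same Discussion says that "this RCT would be the first to study the effects of BLT in the infant". The Background section on BLT and depression during pregnancy describes "Two small (*n* = 10 and *n* = 27) randomized controlled trials among pregnant women with non-seasonal depression", and notes that these earlier studies examined only mood.

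**The infant variables.** Outcome measures lists the birth and child outcomes to be compared between groups: pregnancy duration, birth weight, child behaviour, long-term cortisol exposure and the cortisol response to vaccination. The Covariates section says: "Potential covariates for the infant are head circumference, congenital malformations, Apgar-score and neonatal admission at Neonatal Intensive Care Unit". Under Birth outcomes, "information will be obtained regarding complications during delivery and childbirth from the medical records"; that list includes hospital admission and complications in the first week.

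**The concern.** A conclusion about safety needs safety data. In the abstract the sole condition is efficacy, and the main Discussion presents as settled something the trial is, on its own account, the first to examine. Clinicians and pregnant women choosing between this and other treatments may rely on such a statement.

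The analysis plan makes this harder to put right. Three variables that bear directly on the newborn are named as things to adjust for and are absent from the named outcomes. If BLT affected Apgar score or NICU admission, those variables would lie on the path from treatment to later infant outcomes. Adjusting for them would estimate the effect that remains once that path is blocked, and a harm acting through it would be partly removed from the estimate.

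**Working it through.** **1. Strength of the safety wording.** Three levels appear in one document:
- Adverse effects: no foetal harm is expected (two citations).
- Abstract, Discussion: the treatment will be safe if mood improves; for the child, no reactions are expected.
- Main Discussion: no foetal harm, stated without qualification.

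Nothing in the article moves the claim from the first level to the third. The two randomised trials it describes total 10 + 27 = 37 women in both arms, so fewer than 37 received BLT, and they are described as studying mood only. The size and content of reference 56 are not given.

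**2. Role of the infant variables.**

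| Variable | Named as outcome compared by arm | Named as potential covariate |
|---|---|---|
| Pregnancy duration, birth weight | yes | no |
| Infant behaviour, cortisol exposure, stress response | yes | no |
| Congenital malformations | no | yes |
| Apgar score | no | yes |
| NICU admission | no | yes |

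Women are randomised at 12–18 weeks. Apgar score and NICU admission are determined at or after birth, hence after randomisation. For malformations the timing is less clear, so the over-adjustment argument is made only for the other two.

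**3. What the trial could show.** The plan states no safety figure to reproduce; its sample size rests on depressive symptoms. Inputs from the Randomization and Sample size sections: 150 women at 1:1, so 150 / 2 = 75 per arm, and 63 per arm required.

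If no event of a given kind occurs among n women, the exact one-sided 95% upper limit for its rate is 1 − 0.05^(1/n):
- n = 75: 1 − 0.05^(1/75) = 3.9%
- n = 63: 1 − 0.05^(1/63) = 4.6%

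The zero count is an assumption used to show the best case.

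For events that occur in both arms, the contrast between arms matters more. Power to detect a doubling from p to 2p, by the normal approximation at two-sided 5%, is Φ[(p − 1.96·s0)/s1]. Here s0 = √(2·m(1−m)/75) with m = 1.5p, and s1 = √{[p(1−p) + 2p(1−2p)]/75}. The control risks are assumptions; the article gives none.

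| Assumed control risk | Power, 75 per arm |
|---|---|
| 1% | 7% |
| 2% | 11% |
| 3% | 14% |
| 5% | 21% |
| 10% | 40% |

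Worked line for 5%: s0 = √(2 × 0.075 × 0.925 / 75) = 0.0430; s1 = √[(0.0475 + 0.09)/75] = 0.0428; (0.05 − 1.96 × 0.0430)/0.0428 = −0.80; Φ(−0.80) = 0.21.

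A non-significant difference in such events would therefore say little, which is why confidence intervals are needed.

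**The case against.** **The wording is commentary, not a decision rule.** The article treats safety as a cited premise and efficacy as the open question. The abstract's clause on the child is hedged, and the matching conditional sentence in the main Discussion promises only an alternative treatment. This stands to a degree: a reader might infer that the trial would report safety whatever the data showed, and nothing in the document commits it to that. The hedge does not reach the unqualified sentence in the main Discussion, or the word safe in the abstract.

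**Safety is monitored and partly compared.** Adverse effects belong to the primary aim and are asked about at every measurement. A Data Safety Monitoring Board is in place. Pregnancy duration and birth weight are compared between groups. Hospital admission and first-week complications are collected and may overlap with NICU admission. All of this stands, and it would be wrong to say that foetal and neonatal safety go unexamined.

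**The general analysis rule covers once-measured variables.** The Statistical analysis section says these are compared with a t-test or Chi-Square test, which could include Apgar score, malformations and NICU admission, and the covariates are only potential ones. This is the strongest point. It leaves room for a comparison, but it does not name these items as outcomes and does not remove the role that the Covariates section gives them.

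**Two further inferences are not supported.** A reader might take 37 women as the ceiling of prior evidence, or assume that no foetal events occurred among them. The article also cites reference 56, of unstated size, and reports no foetal event counts. A reader might also fault the birth record list for not naming pregnancy loss. In a condensed article that detail may sit in the full protocol, so its absence is not a finding.

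**Conclusion.** The point holds in a limited form. The main Discussion states foetal safety as fact where the rest of the article supports only an expectation, and the abstract makes safety depend on the mood result alone. Three neonatal variables are assigned a covariate role and no named outcome role; for Apgar score and NICU admission, adjustment could mask a harm.

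On size, the best case of no events among 75 BLT women would exclude only rates above about 3.9%, or 4.6% with 63. Power to detect a doubling of a 1–5% risk is 7–21%. These figures assume full observation of each arm, and the control risks are illustrative. The point about wording and variable roles does not depend on them. It should be corrected, but it does not threaten the primary efficacy analysis.

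**What to change.** 1. **Covariates and Outcome measures.** Take congenital malformations, Apgar score and NICU admission off the covariate list. Name them as neonatal safety outcomes, reported by arm with counts, denominators and 95% confidence intervals, beside the pregnancy duration and birth weight comparisons already planned.
2. **Abstract Discussion and main Discussion.** Reword both so that absence of foetal harm is an expectation, to be judged from these outcomes and the adverse-effect data. Add that no events of a given kind among 75 BLT women would exclude only rates above about 3.9% (one-sided 95% limit).

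**Cost.** Wording changes and one short table. The three items are already foreseen as covariates, so no new data collection should be needed. The downside is a more modest safety statement.

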**Trial registration:**

Netherlands Trial Register NTR5476. Registered 5 November 2015.

## Background

Depression during pregnancy is a common and high impact disease. Approximately 5–10 % of pregnant women suffers from depression [1], which has been confirmed by a study in Rotterdam, the second largest city in the Netherlands [2]. Children who are exposed to maternal depression during pregnancy have a higher risk of adverse birth outcomes, such as low birth weight, and more often show cognitive, emotional and behavioural problems [3–6]. The perinatal period is a critical period, in which epigenetic programming determines not only the perinatal health, but also that of following generations [7]. Therefore, early detection and prompt treatment of depression during pregnancy can benefit both mother and child.

In non-pregnant women, guidelines propose psychotherapy, antidepressant medication or a combination of both as treatment for depression. However, clinical practice shows limited relevance of these guidelines during pregnancy, as the direct availability of psychotherapists is poor, postponing treatment for several months or more. In pregnancy, the window of opportunity is small and from the perspective of the child postponement is in fact non-treatment. Other limitations of psychotherapy are its dependence on good language skills, absence of problems that limit access to therapy and a strong motivation to reflect on ones emotions, cognition and behaviour. These factors limit the applicability of psychotherapy in a majority of pregnant women with depression, who share a socioeconomic deprived background and often have coexisting problems interfering with compliance [8]. Therefore, women with depression during pregnancy may be treated with antidepressants. In North America, use of antidepressants during pregnancy is reported by 5–13 % of pregnant women [9, 10]. In the Netherlands, 2–3 % of pregnant women use antidepressant medication [11, 12]. However, the safety of these medications during pregnancy is controversial [13, 14].

Therefore, investigating non-pharmacological approaches to treating depression during pregnancy is urgent and relevant, for both mother and child. Bright light therapy (BLT) is a promising treatment for pregnant women with depression based on several theoretical and clinical considerations, which will be discussed below.

### BLT and depression

BLT is the first choice treatment for seasonal affective disorder (SAD) [15], a condition of reoccurring depressions during fall and winter, with remissions in spring and summer [16].

The effects of BLT have not only been consistently shown on SAD [16–19], but also on other diseases, such as non-seasonal depression [17], adult attention-deficit/hyperactivity disorder [20] and bulimia nervosa [21, 22]. The effects of BLT on non-seasonal depression have been shown in various populations, like elderly residents of group care facilities and patients with Alzheimer’s disease [23–25].

BLT has been shown to synchronize the biological clock with the environmental day-night rhythm and to shift the circadian rhythm [15, 16]. Evidence suggests that this mediates the effects of BLT on depression, which has been indirectly supported by enhanced sleep and rhythms of melatonin and cortisol [23].

### Hypothalamus-pituitary-adrenal axis

The hypothalamus-pituitary-adrenal gland (HPA) axis is involved in the synchronization of the biological clock by BLT. This axis regulates the secretion of cortisol in response to stress [26]. HPA-axis activity is controlled by the corticotropin-releasing factor (CRF) secreted by parvocellular neurosecretory cells in the paraventricular nucleus (PVN) of the hypothalamus, which activates the secretion of adrenocorticotrophic hormone (ACTH) from the anterior pituitary, which in turn stimulates the production and release of cortisol from the adrenal cortex [26, 27]. CRF and ACTH are both inhibited by cortisol through the glucocorticoid receptor (GR) [26, 27]. Figure 1 shows a schematic overview of this feedback loop.

**Fig. 1 Fig1:**
[figure not shown]
Schematic diagram of the hypothalamus-pituitary-adrenal gland (HPA) axis. Shown are the different structures and hormones involved in the HPA-axis. CRF, produced and released by the hypothalamus, stimulates the anterior pituitary to produce and release ACTH, which in turn stimulates the production and release of cortisol by the adrenal cortex. Cortisol inhibits both the hypothalamus and pituitary through the GR. PVN = paraventricular nucleus; GR = glucocorticoid receptor; CRF = adrenocorticotrophic hormone releasing factor; ACTH = adrenocorticotrophic hormone; + = stimulating; − = inhibiting

The cause of depression is largely unknown. However, the HPA-axis is thought to play a crucial role in the pathophysiology – as cause or consequence, since hyperactivity of this axis is associated with depression. More specifically, depression is thought to be related to reduced inhibition by cortisol, due to impaired GR function [27]. This is supported by a post-mortem study among depressed patients, which showed hyperactivity of CRF neurons of the hypothalamic PVN [28]. Second, increased basal cortisol levels are commonly found in patients with depression [27].

### Suprachiasmatic nucleus

The suprachiasmatic nucleus (SCN), known as the ‘biological clock’, controls the HPA-axis: decreased inhibitory control of the SCN on the HPA-axis has been shown to be associated with HPA-axis hyperactivity [29]. The SCN is located in the hypothalamus on top of the optic chiasm and is the central pacemaker of all physiological and behavioural rhythms [15, 30]. Light is the most powerful environmental signal that synchronizes the SCN with the environmental day-night rhythm (also known as ‘zeitgeber’). Environmental light versus darkness is signalled to the SCN by melanopsin-containing retinal ganglion cells through the retino-hypothalamic tract in the optic nerve (Fig. 2) [15, 31]. The SCN is able to maintain circadian rhythms, even in the absence of zeitgebers [15, 30]. This central control function of circadian rhythms is lost when the SCN is damaged or obliterated. Mice studies have shown that ablation of the SCN results in arrhythmicity [32, 33]. A case report of a patient with hypothalamic damage demonstrated disturbances in the sleep-wake cycle, body temperature and cognitive and behavioural functioning [34].

**Fig. 2 Fig2:**
[figure not shown]
Sagittal view of the brain. This figure shows a sagittal view of the suprachiasmatic nucleus, the optic chiasm, the optic nerve, the hypothalamus, the pituitary and the pineal gland

### Melatonin

Melatonin is, next to cortisol, influenced by light. Melatonin is produced and secreted by the pineal gland and, like other circadian rhythms, its rhythm is controlled by the SCN (Fig. 2) [35, 36]. Typically, melatonin levels rise in the evening, peak at early morning hours and drop to baseline at awakening [26]. Light inhibits the production of melatonin [26].

Different studies showed a change in melatonin secretion in psychiatric diseases, such as a reduction of melatonin secretion in depression [35, 37]. Earlier, BLT in the morning has been shown to normalize saliva melatonin evening levels in elderly patients with a depressive disorder [23].

Melatonin concentrations increase during the course of pregnancy [36]. However, a study showed that nocturnal melatonin levels were lower in depressed pregnant women, compared to healthy controls [38]. In this study, we want to explore the effects of BLT on evening and morning melatonin levels.

